#### Sensory testing

Sensitivity and preferences of sweet and fat taste are assessed. Participants rate the intensity and hedonic preference of five sucrose and dairy samples on a general labelled magnitude scale (gLMS) (Bartoshuk et al. 2004; Lim et al. 2008).

#### Physical activity

A w-GT3X triaxial accelerometer (Actigraph, Pensacola, FL) secured to a waist belt, is worn for seven days, with a minimum of 10 h per day, to measure all components of physical activity and energy expenditure. Participants maintain their regular physical activity, whilst keeping a diary of times when the device is not worn. At least three full week and two weekend days is required for analysis. Physical activity counts will be calculated from raw data as the square root of the sum squared of activity counts, and will be categorized using metabolic equivalents (METs), as defined by the American College of Sports Medicine guidelines (Pescatello and American College of Sports Medicine 2014). Activities will be classified as light or sedentary (1.1-2.9 METs), moderate (3.0-6.0 METs), or vigorous (>6.0 METs). A physical activity diary is kept to record periods of non-wear and of intentional exercise. A self-reported RPAQ (Besson et al. 2010) is completed at the end of seven days with reference to the previous four weeks, allowing, together with the diary, a specific interpretation of the accelerometry counts.

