#### Assessments (stages 2 and 3)

Participants recruited in stage 1 are invited to the research unit within 14 days of the start of their last menstrual period (the follicular phase) for testing to avoid the confounding effect of menstrual cycle hormones on taste perception, energy intake and energy expenditure (Davidsen et al. 2007).

Stage 2 of testing involves measurements of anthropometry, body composition, metabolic health, dietary intake, taste perception, and eating behaviour, which are described in detail below.

Stage 3 of assessment is completed at home over a seven day period. Participants wear accelerometers and keep a physical activity diary to assess physical and sedentary activity objectively in real life. At the end of the seven days, participants complete the RPAQ and the dietary diversity questionnaire (DDQ) (see Figure 1).

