Diet Quality	Eating Habits Questionnaire	Developed in this study	-	Dietary habits
				- eating habits
				- meal distribution
				- food choices.
Dietary Variety	Dietary Diversity Questionnaire (DDQ)	Developed in this study; mostly based on foods in the FFQ	-	Dietary diversity
				Food variety.
Dietary Behaviour	Three Factor Eating Questionnaire (TFEQ)	(Stunkard and Messick 1985)	-	Dietary behaviour
				- Restraint,
				- Disinhibition,
				- Hunger.
Physical Activity patterns	-	(Pescatello and American College of Sports Medicine 2014)	WGT3X Actigraph	Objective real life physical activity
				Physical activity expenditure
				- sedentary activities
				- intensity of activity.
	Physical Activity diary	-	-	Self-reported accelerometer non-wear time
				Self-reported intentional exercise
				– time
				- duration
				- type
				- intensity.
Physical Activity behaviour	Recent Physical Activity Questionnaire (RPAQ)	(Besson et al. 2010)	-	Self-reported physical activities
				- sedentary activities
				- time
				- intensity.
Taste perception, intensity, and hedonic preference	-	(Lim et al. 2008; Bartoshuk et al. 2004)	Rate intensity and hedonic preference of sweet and fat taste on a gLMS.	Sweet and fat taste sensitivity and preference.

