## Discussion

An ethnic-specific focus aimed at weight maintenance has been recommended from previous NZ research (Metcalf et al. 2000). Overweight or obesity is a continual process and the effects of inappropriate lifestyle behaviour may often be missed when strictly assessing BMI as an indicator of over-nutrition. BMI provides only a crude measure of body fatness as it does not distinguish between weight associated with muscle or with fat. However, it appears to remain a useful estimate of the proportion of the population with increased risk of health conditions associated with obesity (World Health Organisation 2000), but may not be able to predict disease risk in those with normal BMI and varying adiposity.

Previous research has shown that a significant proportion of individuals with normal weight and subsequent normal BMI values had excessive body fat or “hidden” fat (Kruger et al. 2010a; De Lorenzo et al. 2006; Romero-Corral et al. 2010; Kruger et al. 2010b). This “hidden fat” profile may be linked with early inflammation and may be a key factor in the emerging epidemic of obesity and related disease risk (De Lorenzo et al. 2006; De Lorenzo et al. 2007). Pilot study data from our laboratory (Kruger et al. 2010a; Kruger et al. 2010b) revealed that in a free-living population (N = 116) of 18 to 44 year old NZ European women, 21.4% had a “hidden fat” profile and subsequent increased metabolic disease risk (identified through elevated fasting plasma leptin and insulin concentrations) and higher levels of sedentary lifestyle parameters.

Although a few studies have explored normal weight obesity (Marques-Vidal et al. 2008; Di Renzo et al. 2010; Romero-Corral et al. 2010; Karelis et al. 2004), not many studies have been specifically conducted to explore metabolic disease risk associated with high body fat (hidden or apparent), in premenopausal women. The typical central fat deposition following menopause and/or ageing may be absent in premenopausal women, despite the fact that women steadily gain weight from menarche to adulthood. It is therefore unclear where the hidden fat is situated in these women, especially if they are slender. It may be that excess fat in a lean person is hidden in the abdomen or elsewhere where it could pose health risks and cause metabolic dysregulation (Di Renzo et al. 2006; Huxley et al. 2010; Martinez et al. 2008; Cameron et al. 2009).

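### The accelerometer classes merge sedentary with light activity and omit wear time below 1.1 METs, so as written they give no separate objective sedentary variable

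*Protocol article*

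**What the plan says.** The Physical activity section of the protocol article describes a waist-worn triaxial accelerometer, worn for seven days, "to measure all components of physical activity and energy expenditure". The processing starts from the device recordings: "Physical activity counts will be calculated from raw data as the square root of the sum squared of activity counts". The rule for intensity classes follows: "Activities will be classified as light or sedentary (1.1-2.9 METs), moderate (3.0-6.0 METs), or vigorous (>6.0 METs"). No other accelerometer threshold appears in the article.

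Two other places state what the device is for. The section on assessments in stages 2 and 3 says: "Participants wear accelerometers and keep a physical activity diary to assess physical and sedentary activity objectively in real life". In Table 1, the Actigraph row gives the concept captured as "Objective real life physical activity", and under it lists "sedentary activities" on a separate line from intensity of activity. Table 1 lists sedentary activities again for the RPAQ, which is self-reported.

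The Background makes dietary and physical activity patterns, as predictors of body composition profile, one of the primary outcomes. The Discussion reports that pilot participants with the hidden fat profile had increased metabolic risk "and higher levels of sedentary lifestyle parameters".

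**The concern.** The article promises an objective measure of sedentary activity and then states a coding rule that does not produce one. The label sedentary is attached to a band that also holds all light activity. The band starts at 1.1 METs, so the quietest wear time falls in no class.

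Activity pattern is a primary predictor domain, and sedentary behaviour is the lifestyle difference that the article reports from its own pilot. If the rule is followed literally, a difference between profiles in sitting time may not show in the class totals, or may show in a direction that contradicts the label. The remaining named sedentary measure would be the RPAQ, which relies on recall over the previous four weeks and so does not stand in for the objective measure.

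**Working it through.** The article gives no figure to reproduce here. The check is to apply the stated rule and compare the result with the stated purpose.

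**Step 1: apply the rule to test values.** The only inputs are the class limits in the Physical activity section.

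| METs | Class under the rule |
|---|---|
| 0.9, 1.0, 1.05 | none |
| 1.1, 1.3, 1.5, 1.6, 2.0, 2.5, 2.9 | light or sedentary |
| 3.0, 6.0 | moderate |
| 6.1 | vigorous |

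No class contains sedentary time alone, and nothing below 1.1 METs is classified. An unrounded value such as 2.95 also falls between classes, but that is only a matter of rounding.

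**Step 2: compare with the purpose.** The Stage 3 description and the Actigraph row of Table 1 each name sedentary activity as something the device captures. Table 1 separates it from intensity. The rule yields three intensity totals, and none of them is a sedentary total.

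**Step 3: see what the pooled class does when sitting is replaced by light activity.** Let S be minutes of sitting, L minutes of light activity at 1.1 to 2.9 METs, M moderate, V vigorous and W wear time. Move 60 minutes a day from S to L, with M, V and W fixed. The 60 minutes is an illustration and does not come from the article.

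- *Sitting scores 1.1 METs or more.* The class total is S + L. After the move it is (S − 60) + (L + 60) = S + L. The change is 0 minutes.
- *Sitting scores about 1.0 MET.* The class total is L. After the move it is L + 60. The change is +60 minutes, although the woman sits 60 minutes less.
- *Mixed case.* If a share p of the moved sitting minutes scores 1.1 METs or more, the change is 60 − 60p = 60(1 − p) minutes, which lies between 0 and +60.

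The article does not say how sitting would score, so p is unknown. For no value of p does the light-or-sedentary total fall when sitting falls.

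**Step 4: check whether unclassified wear time fills the gap.** The residual is W minus the three class totals. If all sitting scores below 1.1 METs (p = 0), the residual equals S. If all of it scores 1.1 METs or more (p = 1), the residual holds no sitting. In between it holds only part. The residual is therefore a sedentary measure only under an assumption that the article does not make, and it runs against the article's placing of the label sedentary at 1.1 to 2.9 METs.

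**The case against.** The strongest reply is that this is a coarse label and not a loss of information. Much of that stands.

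- A reader might infer that objective sedentary time cannot be analysed at all. The article does not support this. Counts are derived from raw data, so a sedentary threshold can be applied later. Time below 1.1 METs can be recovered as residual wear time, because non-wear is recorded in a diary.
- A reader might infer that the objective data are wholly insensitive to replacing sitting with light activity. The zero change holds only if sitting scores 1.1 METs or more. It also concerns one derived total: the accelerometer is to yield counts and energy expenditure as well, and the rule does not touch these.
- A reader might infer that the comparison suggested by the pilot has been removed. The Discussion does not say how the pilot's sedentary parameters were measured, or whether they were separated from light activity. The RPAQ still gives self-reported sedentary time, and the article plans to interpret the counts together with the RPAQ and the diary.
- The statistical analysis section refers to physical activity patterns and does not say that these three class totals are the model variables. How patterns are built may be set out in a fuller document.
- The class limits are referred to a cited guideline that is not at hand and may use these bands.

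The last two replies do not remove the point. The article does not leave the classes open. It states a specific rule, and that rule does not deliver what the Stage 3 description and Table 1 say is captured. Whatever the guideline says, the article's own sections still disagree.

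**Conclusion.** The point holds as an inconsistency between a stated coding rule and the stated purpose of the measurement. Under the classes as written, there is no separate objective sedentary variable in a primary predictor domain. Moving 60 minutes from sitting to light activity changes the light-or-sedentary total by between 0 and +60 minutes, depending on how sitting scores, and never lowers it.

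This rests on two readings: that the three classes are meant to summarise the accelerometer record, as the Physical activity section says, and that no other sedentary threshold is in use, since none is given. It does not rest on any particular sedentary cut-point. It should be corrected before analysis, but it is a variable definition that can be repaired from recorded data. Sample size, power and error rates are unaffected.

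**What to change.** Replace the three-class rule with exhaustive, non-overlapping classes that cover all wear time, including time at or below 1.0 MET. Separate sedentary from light at a cut-point stated before the analysis. The article gives no value for it, so the choice and its justification are for the investigators. Fixing it in advance avoids the criticism that it was chosen after seeing group differences. Analyse sedentary and light time as separate variables and account for wear time. Bring the Physical activity section, the Stage 3 description and the Actigraph row of Table 1 into line with the new definition.

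The cost is re-coding existing accelerometer files. Participants have nothing further to do, and no new data are needed.

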### Data handling and statistical analysis

Statistical analysis will be performed using IBM SPSS statistics (IBM Corporation, New York, USA). Descriptive statistics will be used to describe the baseline population using mean (standard deviation), median (25, 75 percentile) or frequencies summary statistics. Normality of distribution will be evaluated using the Kolmogorov-Smirnov test and examining normality plots. Non-normally distributed variables will be transformed into approximately normal distributions by logarithmic transformations and again tested for normality. Primary statistical analyses will involve ANOVA tests with post-hoc analysis and Bonferoni adjustments comparing body composition profile groups regarding metabolic disease risk markers and dietary and physical activity patterns and miRNA levels; multiple logistic regression analysis to determine odds ratios of having a “hidden body fat” profile based on dietary and physical activity patterns; and, separately, miRNA expression levels. Principal components analysis will be performed on the miRNA data using the PCP directive in GenStat to identify linear combinations of the miRNAs that account for most of the variation between individuals (Zacharewicz et al. 2014); and Pearson correlations to determine correlation coefficients between dietary and physical activity patterns and miRNA expression profiles. A p-value of <0.05 will be considered significant.

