## Methods/Design

### Study design

The Women’s EXPLORE (“EXamining Predictors Linking Obesity Related Elements”) is a cross-sectional study targeting post-menarcheal, premenopausal NZ women to examine predictors of body composition profiles. Three body composition profile groups will be explored, namely:

“Normal Fat” group – normal BMI (<25 kg/m^2^), normal BF% (≥22%,<30%);

“Hidden Fat” profile group – normal BMI (<25 kg/m^2^), high BF% (≥30%);

“Apparent Fat” profile group – high BMI (≥25 kg/m^2^), high BF% (≥30%) (Oliveros et al. 2014; Okorodudu et al. 2010; NHLBI Obesity Education Initiative Expert Panel on the Identification Evaluation and Treatment of Overweight and Obesity in Adults 1998).

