### Participants and sample size

Study participants are adult NZ women from three ethnic groups (NZ European, Māori, and Pacific Island). A total sample size of 225 women per ethnic group, consisting of 75 per profile group, will provide 80% power at significance levels of p < 0.05 to detect a medium effect size *f* of 0.25 (G*Power 3.1.2) for comparing the “hidden fat” profile with the other two body composition profiles (“normal fat” and “apparent fat”) regarding metabolic disease risk markers, dietary and physical activity patterns, and miRNA expression levels.

The medium effect size is relevant to all variables, and encompasses a variety of scenarios, as we wish to be able to explore how metabolic profile changes with body composition. For example, if the three groups have equally spaced means (μ - Δ, μ, μ + Δ), the difference in means will be detected with 80% power when Δ = 0.31 x σ, where σ is the within group standard deviation. For cholesterol, where preliminary data suggests σ = 0.98 mmol/L, we have 80% power to detect the difference when Δ = 0.30 mmol/L. Alternately, if two groups have the same mean μ and the third has mean μ + Δ, 80% power is achieved when Δ > 0.53 x σ, or 0.52 mmol/L in the case of cholesterol. A Δ = 0.30 – 0.52 mmol/L is estimated to be associated with a 9 – 15% lower relative risk of coronary heart disease (CHD)-related mortality (Gould et al. 2007). For HDL-C where preliminary data suggests σ = 0.38 mmol/L we have 80% power to detect a difference when Δ = 0.12 – 0.20 mmol/L. Every 0.1 mmol/L increase in HDL-C has been suggested to reduce CHD risk by between 8 – 15% (Gordon et al. 1989; Turner et al. 1998). For TG where preliminary data suggests σ = 0.45 mmol/L we have 80% power to detect a difference when Δ = 0.14 – 0.24 mmol/L. Studies in women showed a 1 mmol/L increase in TG was associated with 37% increase in risk of CVD (after adjustment for HDL-C and other risk factors)(Austin et al. 1998); Δ of 0.14 – 0.24 is thus estimated to be associated with 5.2 – 9% difference in CVD risk.

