The power for simple (one variable) logistic regression for the risk of having a “hidden fat” profile among people of normal BMI is equivalent to the power of the independent sample t-test (Vaeth and Skovlund 2004) for comparing the predictor variable mean between the hidden fat and normal fat profiles. With a sample size of 75 per group and equal variance within groups, 80% power is achieved for differences of 0.46 σ. For instance, preliminary data on total energy expenditure assessed using the Recent Physical Activity Questionnaire (RPAQ) estimates the standard deviation at 5.36 METs-h/day; if the true difference means between the body composition groups is 2.47 METs-h/day, the logistic regression coefficient will be significantly non-zero 80% of the time. Clinically, the difference of 2.47 METs-h/day equates to ~684 kJ/day (164 kcal/day)(Besson et al. 2010), which is considered within the target range of recommended energy expended each day in physical activity and/or exercise (Pescatello and American College of Sports Medicine 2014). We will consider logistic regression predictors from the dietary and activity pattern data, and separately for the miRNA measurements.

Based on our pilot study that showed a prevalence of 21% of NZ European women having a “hidden fat” profile, (Kruger et al. 2010b) a sample of ~1140 women will need to be screened (380 per ethnicity) to find ~75 women per profile group; or to explore new profiles. The study design and study procedures are illustrated in Figure 1.

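### For three profile groups, the Bonferroni-adjusted post-hoc tests are valid but inefficient: a closed test keeps 5% family-wise error per marker and adds about 8 to 16 points of power

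*Protocol article*

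**What the plan says.** The protocol article's Study design section defines normal, hidden and apparent fat profiles: "Three body composition profile groups will be explored". The sample size section plans "A total sample size of 225 women per ethnic group, consisting of 75 per profile group" and gives as its purpose a comparison of hidden fat with each of the other two: "for comparing the “hidden fat” profile with the other two body composition profiles".

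For the analysis, Data handling and statistical analysis states: "Primary statistical analyses will involve ANOVA tests with post-hoc analysis and Bonferoni adjustments comparing body composition profile groups". The threshold is "A p-value of <0.05 will be considered significant". The text does not say how many comparisons the Bonferroni adjustment covers, whether the pairwise tests wait for a significant F, or whether the ANOVA is run within each ethnic group.

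For the single-predictor logistic model of hidden versus normal fat, the sample size section says: "With a sample size of 75 per group and equal variance within groups, 80% power is achieved for differences of 0.46 σ". That figure carries no multiplicity adjustment.

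**The concern.** The main hypothesis is that hidden fat carries higher metabolic risk, so hidden versus normal fat is a key contrast. Bonferroni over three pairs tests it at 0.05/3 = 0.0167. With exactly three groups this is stricter than 5% family-wise control requires:

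- If all three means are equal, no pair can be declared different unless the 5% overall test rejects.
- If exactly one pair is equal, only one false rejection is possible, and that pair is tested at 5%.
- If no pair is equal, no false rejection can occur.

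An overall test followed by unadjusted pairs (Fisher's protected test) is therefore a closed procedure for three groups. Any pair rejected by an F test plus Bonferroni is rejected by it too. What is at stake is power for the contrasts the study was sized for, at no cost in participants.

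**Working it through.** **Inputs from the protocol article.** Three profiles; 75 per profile within an ethnic group; alpha 0.05; effects of 0.31 SD (equally spaced means), 0.53 SD (one group different) and 0.46 SD (hidden versus normal).

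**Assumptions.** Two-sided pairwise tests, Bonferroni over three pairs, analysis within one ethnic group and, for the main table, equal variances.

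**1. The protocol's own figure.** For two groups of 75 at 0.46 SD, the standard error is √(2/75) = 0.1633 SD and the noncentrality is 0.46/0.1633 = 2.82. On 148 df, two-sided 5%, power is 79.9%. The stated 80% reproduces.

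**2. Critical differences.** With the pooled ANOVA variance, df = 225 − 3 = 222.
- Unadjusted: t = 1.971, so 1.971 × 0.1633 = 0.322 SD.
- Bonferroni over three pairs: t = 2.412, so 2.412 × 0.1633 = 0.394 SD.

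By the noncentral t at 0.46 SD, pairwise power is 80.1% unadjusted and 65.7% with Bonferroni.

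**3. Power for hidden versus normal.** Simulation, 400,000 draws per scenario:

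| Scenario | F then Bonferroni (3 pairs) | F then unadjusted pairs | Gain (points) |
|---|---|---|---|
| 0.31 SD, equally spaced | 30.6% | 46.9% | 16.3 |
| 0.46 SD, apparent equal to hidden or to normal | 65.7% | 75.8% | 10.1 |
| 0.46 SD, equally spaced | 65.8% | 80.1% | 14.3 |
| 0.53 SD, one group different | 79.7% | 87.6% | 7.9 |

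Over the protocol's own effects the gain is about 8 to 16 points.

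**4. Family-wise error for one marker.** The closed test gives 5.0% with all means equal and about 5.0% with one group different. F then Bonferroni gives 4.2% and 1.7%.

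**5. Other readings of the text.**
- Bonferroni over only the two hidden-fat contrasts (0.025 each): the gain is about 4 to 11 points.
- Ethnic groups pooled, 225 per profile: at 0.31 SD equally spaced, 81.3% becomes 90.8%, a gain of 9.5 points. At 0.46 SD with apparent equal to hidden, 99.3% becomes 99.8%, a gain of under 0.5 point.

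**6. Unequal variances (assumed SDs 1, 1, 1.5, the largest in apparent fat).** With pooled variance, the closed test's error is 5.3% with all means equal and 6.8% when only hidden equals apparent. A Welch F followed by unadjusted Welch t tests gives 5.0% with all means equal and 4.9-5.0% with one pair equal. Hidden-versus-normal power at 0.46 SD is then 73-80%, against 65% for Welch tests with Bonferroni.

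**The case against.** **Bonferroni after ANOVA is valid, and nothing in the analysis section is wrong.** This stands. The point is about efficiency only.

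**The closed test depends on exactly three groups.** This stands as a limit on the fix. The sample size section allows for new profiles to be explored, and there are nine profile-by-ethnicity cells. With one group far from the rest, F then unadjusted pairs has 12.1% family-wise error with four groups (Bonferroni 2.2%) and 51% with nine cells (3.0%).

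**Equal variances are not secured.** The apparent fat group has no upper limit on BMI or body fat, so a wider spread there is plausible. The pooled version can exceed 5%; the Welch version does not in the case checked.

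**Stronger readings that the protocol does not support:**

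- A reader might infer that the F test and Bonferroni together are a double penalty. The text does not say that the pairwise tests are gated. If they are, the gate costs Bonferroni less than 0.3 point in these scenarios; the loss comes from Bonferroni itself.
- A reader might infer that Bonferroni buys no error protection. Its actual error is lower, at 1.7-4.2% against 5%. It buys more than the 5% level requires. Many markers are tested at 0.05 and the section states no other adjustment, so some may value that margin.
- A reader might infer that the ANOVA and the logistic analysis would give opposite verdicts on one contrast because one is adjusted and the other is not. The planned analysis is multiple logistic regression, which can differ from the ANOVA under any adjustment. It uses diet, activity and miRNA predictors, so it does not test the metabolic-risk hypothesis. The single-predictor model appears only in the power calculation.

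**Conclusion.** The point holds as an optional improvement that is cheap to make. Within one ethnic group, with 75 per profile and Bonferroni over three pairs, a three-group closed test keeps 5% family-wise error per marker and raises hidden-versus-normal power by about 8 to 16 points at the protocol's planning effects. The size depends on readings the article does not fix; on other readings it is smaller, and close to nil at 0.46 SD if the ethnic groups are pooled. The 66% under Bonferroni does not make the stated 80% wrong: that figure refers to an unadjusted single-predictor comparison and reproduces. Neither method controls error across markers or across the three ethnic groups.

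**What to change.** In Data handling and statistical analysis, replace the Bonferroni post-hoc wording with a rule along these lines:

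- For each marker within each ethnic group, compare the three profiles with an overall test at 5%, using the Welch F if variances may differ.
- Only if it is significant, test each pair at an unadjusted 5% with the same variance model (Welch t with Welch F).
- State that this holds only for exactly three groups. Keep Bonferroni or Holm if a further profile is added or if profile-by-ethnicity cells are compared.
- Report each pairwise difference with a 95% confidence interval.

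The cost is a few lines of text and no additional women. The downsides should be stated: the pairwise intervals are no longer simultaneous, the actual error per marker rises from 1.7-4.2% to the nominal 5%, and error across markers and ethnic groups stays uncontrolled, as it is now.

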This study will be conducted as a cross-sectional comparative designed study. The primary aim of this study is to explore the metabolic risks and predictive factors associated with the hidden and apparent body fat profiles in 16 to 45 year old (post-menarcheal and premenopausal) NZ European, Māori and Pacific women. The primary outcomes are:Investigating the association between body composition profiles and markers of metabolic disease risk, including glucose, lipid and inflammatory marker profiles;Investigating dietary and physical activity patterns as predictive factors associated with body composition profiles;Investigating miRNA expression related to energy expenditure/storage as a predictive factor associated with body composition profiles.

The secondary outcomes are:Investigating associations/interactions between dietary and physical activity patterns and miRNA expression and how this may modulate the odds of having a specific body composition profile;Investigating taste perceptions as a predictive factor associated with the different body composition profiles;Investigating eating behaviour and habits as predictive factors associated with the different body composition profiles;Investigating nutrient intake as a predictive factor associated with the different body composition profiles.

We hypothesise that the “hidden fat” profile is associated with increased metabolic disease risk in NZ European, Māori, and Pacific women aged 16 to 45 years. We further hypothesise that for all women, dietary and physical activity patterns are predictors of a particular body composition profile by modulating miRNAs associated with energy expenditure/storage.

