**Study design and procedures.**

Inclusion criteria for women are:age (16 to 45 years),being post-menarcheal or pre-menopausal (as defined by a continuous regular menstrual cycle for the past one complete year),ethnicity (being of NZ European, Māori, or Pacific ethnicity as defined by self-identification and having at least one parent from the same ethnicity).

Exclusion criteria for women are:pregnancy and lactation,presence of any diagnosed chronic illness particularly affecting metabolic health (e.g. T2DM),presence of dairy allergy as the taste solution is dairy based.

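### The stated primary profile comparisons do not adjust for age in women aged 16 to 45, so age may confound the association between body fat profile and metabolic markers

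*Protocol article*

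**What the plan says.** Under Data handling and statistical analysis, the protocol article states: "Primary statistical analyses will involve ANOVA tests with post-hoc analysis and Bonferoni adjustments", used for "comparing body composition profile groups regarding metabolic disease risk markers and dietary and physical activity patterns and miRNA levels". The only adjustment named is for multiplicity. The same paragraph plans "multiple logistic regression analysis to determine odds ratios of having a “hidden body fat” profile based on dietary and physical activity patterns" and, separately, a model on miRNA expression. Age is not among the predictors named for either model.

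The sample size section rests on comparisons of the same unadjusted kind. It uses a three-group effect size f of 0.25 with 75 women per profile in each ethnic group. For one-variable logistic regression it treats power as that of a two-sample t-test, with a detectable difference of 0.46 SD.

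The design is described as follows: "This study will be conducted as a cross-sectional comparative designed study". Study design defines the profiles by BMI and body fat percentage alone. Eligibility runs from 16 to 45 years, and group targets are set by ethnicity and profile. No age matching, stratum or quota is stated.

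On age and body size, the Discussion says that "women steadily gain weight from menarche to adulthood", and the Background describes weight gain between 15 and 35 years. The main hypothesis is that the hidden fat "profile is associated with increased metabolic disease risk in NZ European, Māori, and Pacific women aged 16 to 45 years".

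**The concern.** A woman's profile is something she has, not something she was allocated to. If the profiles differ in mean age and a marker also varies with age, a comparison on profile alone credits the age difference to the profile. The article gives its own reason to expect some age difference, since weight rises over much of the eligible range.

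At stake is how the main hypothesis is read. An apparent link between hidden fat and metabolic risk could be partly a link with age. A larger sample does not remove this bias; it only makes a biased difference more likely to reach significance. The logistic models have the same weakness if diet, activity or miRNA levels vary with age.

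**Working it through.** **The plan's own pairwise figure.** With 75 per group, two-sided 5% and a difference of 0.46 SD, the noncentral t gives 79.9% power. The stated 80% is reproduced, so 0.46 SD is the right yardstick for hidden versus normal fat.

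**Assumptions.** The article gives no mean ages, age SD or marker-age correlations. I assume:
- a hidden-versus-normal age gap g of 0 to 0.5 SD of age (0.5 SD is 4 years if the age SD is 8; an even spread over 16 to 45 would give about 29/√12 = 8.4 years);
- a within-profile correlation r of marker with age of 0.1 to 0.3;
- no true difference between the profiles.

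**Bias.** The spurious difference in marker SDs is g × r. The chance of a false hidden-versus-normal finding follows from the noncentral t with noncentrality g × r × √(75/2). Three pairwise contrasts give a Bonferroni level of 0.05/3 = 1.67%.

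| g | r | Spurious difference (SD) | Share of 0.46 SD | Rejection at 1.67% | Rejection at 5% |
|---|---|---|---|---|---|
| 0 | any | 0 | 0% | 1.7% | 5.0% |
| 0.25 | 0.1 | 0.025 | 5% | 1.8% | 5.3% |
| 0.25 | 0.3 | 0.075 | 16% | 2.8% | 7.4% |
| 0.5 | 0.1 | 0.05 | 11% | 2.2% | 6.1% |
| 0.5 | 0.2 | 0.10 | 22% | 3.8% | 9.3% |
| 0.5 | 0.3 | 0.15 | 33% | 6.9% | 15.0% |

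For total cholesterol, with the stated SD of 0.98 mmol/L, the largest spurious difference is 0.15 × 0.98 = 0.15 mmol/L. The sample size section calls 0.30 to 0.52 mmol/L detectable.

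**If ethnic groups were pooled.** With 225 per profile, the last two rows become 9.1% and 21.0% at the 1.67% level. The article powers the comparison within each ethnic group and does not state pooling, so these figures are conditional.

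**Cost of adjusting.** Adding age removes a share r² of the residual variance but loses some information because age and profile overlap. The effective size per group is 75 × (1 − ρ²)/(1 − r²), where ρ² = (g²/4)/(1 + g²/4). At g = 0.5, ρ² = 0.0625/1.0625 = 5.9%. Power for 0.46 SD at two-sided 5%:
- g = 0, r = 0.3: effective 82.4 per group, power 84%;
- g = 0.5, r = 0.3: effective 77.6, power 81%;
- g = 0.5, r = 0.1: effective 71.3, power 78%;
- a harsher case, a 5-year gap with age SD 8 (g = 0.625) and r = 0: effective 68.3, power 76%.

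The range is therefore about 76% to 84%, against 80% unadjusted.

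**The case against.** The best counter-argument is that this is a one-paragraph journal summary. It never says the analyses are unadjusted, and covariate lists are commonly left to an analysis plan that is not shown here. That stands as a caution: age control is not stated, which is less than saying it is ruled out, and the study design figure is not available. It does not dispose of the point. The article names the primary method and the predictors of its models, and the sample size section is built on the same comparisons. A reader will take these as the prespecified analysis.

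A second objection also has force. Hidden and normal fat both require a BMI below 25, so women who gain weight would tend to move into the apparent fat group. The weight-gain remarks therefore support an age difference mainly for apparent fat. For hidden versus normal fat the age difference is plausible but not shown, and neither its direction nor its size is documented.

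Third, the article speaks of association, and it excludes diagnosed chronic illness and requires regular cycles, which may remove some age-related differences.

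A reader might infer that the hidden-fat result would be wholly an age effect, or could not be interpreted at all. The documents do not support that: the bias ranges from nothing to about a third of the detectable difference. Nor should the bias be set against 0.31 SD, which is the step between adjacent groups in the three-group scenario rather than the pairwise figure.

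**Conclusion.** The point holds in a moderate form. As stated, the primary comparisons leave age uncontrolled in an observational contrast spanning ages 16 to 45, and a better method is available using a variable needed for eligibility. The spurious hidden-versus-normal difference is 0 to 0.15 SD, and the per-contrast error at 75 per profile goes from 1.7% to at most about 7%. Both figures rest wholly on the assumed age gap and correlations, and at the low end the effect is negligible. The error would be higher only with a larger gap or correlation than assumed, or if ethnic groups were pooled. The case for changing the model rests on the design and on the low cost of adjusting, not on evidence that the profiles do differ in age.

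**What to change.** State the primary comparison as a linear model (ANCOVA) of each marker, on the log scale where needed, on profile and age, adding ethnicity if ethnic groups are pooled. Take the Bonferroni contrasts on the age-adjusted means. Add age, and ethnicity if pooled, to each logistic model. Report the unadjusted ANOVA alongside so that the effect of adjustment can be seen. A quadratic age term is optional.

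The cost is a change of wording and one or two degrees of freedom. No new participants or measurements are needed. Power for 0.46 SD could fall slightly or rise slightly, within the 76% to 84% shown above.
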